#### Sample Size Considerations and Calculation

We expect a prevalence of 15% for alcohol use disorder, 25% for anxiety and depression and 40% for PTSD in the Ukrainian population based on the available prevalence data in Ukraine and on data from other conflict areas [11]. Sample size requirements are highest for a prevalence of 40%, on which we thus base sample size calculations. We consider a specific age group in a specific cluster (e.g., participants 25–44-year-old in a specific cluster of oblasts) as the unit for which we need a certain precision to estimate prevalence. To provide a precision of ±5% in estimating prevalence with 95% confidence intervals for a specific age group in a specific cluster, the required sample size is 369 survey respondents per combination of age group and cluster. Assuming a potential attrition of 15% among those who consent to participate, the required sample size for enrolment is 435 per age and cluster stratum. The size of the target sample is 5,220 persons (net sample; given 4 age and 3 cluster of oblasts strata). Considering a participation rate of approximately 7% for MAP-U, reflecting the difficult situation in Ukraine, the final number to be randomly drawn from the population registry in Ukraine is 1,740 per stratum and 74,570 for the total sample, respectively. For the MAP-Z study, a participation rate of 25% is assumed based on experiences with previous population-based studies in the canton of Zurich (e.g., Corona Immunitas studies). For the age groups of 25–44 and 45–64 years in people living with protection status S as well as for all four age groups of the general population of the canton of Zurich we will also have 435 participants per age group, or 1,740 people to be invited initially. But there are less than 1,740 people with protection status S in the youngest (18–24 years) and oldest (65+ years) age group with protection status S in Zurich. Thus, we will aim for randomly selecting 684 people in those two age groups in order to have 171 (25%) finally included. In these age groups, the precision will be lower, and 95% CI expected at ±8%. The total sample sizes for people living with protection status S and for the general population living in the canton of Zurich will thus be 1220 and 1740, respectively.

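### The MAP-U draw of 1,740 per stratum contradicts the 7% participation rate and the 74,570 total, which both require about 6,214 per stratum

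*Protocol article*

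**What the plan says.** All the relevant figures are in the protocol article, under Sample Size Considerations and Calculation.

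- Basis: "Sample size requirements are highest for a prevalence of 40%, on which we thus base sample size calculations".
- Precision target: "To provide a precision of ±5% in estimating prevalence with 95% confidence intervals for a specific age group in a specific cluster".
- Respondents: "the required sample size is 369 survey respondents per combination of age group and cluster".
- Attrition and enrolment: "Assuming a potential attrition of 15% among those who consent to participate", "the required sample size for enrolment is 435 per age and cluster stratum". With 4 age groups and 3 clusters, the net MAP-U sample is given as 5,220.
- Participation: "Considering a participation rate of approximately 7% for MAP-U, reflecting the difficult situation in Ukraine".
- Resulting draw: "the final number to be randomly drawn from the population registry in Ukraine is 1,740 per stratum and 74,570 for the total sample".

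A few lines later the same section turns to MAP-Z, where participation is assumed to be 25%. For the age groups with enough people it says "we will also have 435 participants per age group, or 1,740 people to be invited initially".

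**The concern.** The MAP-U sentence gives a draw per stratum and a total draw, and the first multiplied by the number of strata does not give the second. The per-stratum figure also does not follow from the participation rate stated in the same sentence, although it is exactly the figure that follows from the MAP-Z rate.

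This is more than a slip in background text. MAP-U sampling is age-stratified, and the section names the age-by-cluster cell as the unit in which a given precision is needed. A per-stratum count is what someone drawing the sample would naturally work from. A count too small by a factor of 3.6 would miss the enrolment target and the ±5% precision in every cell, and subgroup prevalence by cluster and age group is a planned analysis.

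**Working it through.** **Inputs** (all from Sample Size Considerations and Calculation): prevalence 40%; half-width 5% at 95% confidence; attrition 15%; 4 × 3 = 12 strata; participation about 7% for MAP-U and 25% for MAP-Z.

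**Step 1. Reproduce the plan's own chain.**

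- Respondents per stratum: n = z²p(1−p)/d² = 1.96² × 0.40 × 0.60 / 0.05² = 368.8, rounded up to 369. Agrees.
- Enrolled per stratum: 369/(1 − 0.15) = 434.1, rounded up to 435. Agrees.
- Net total: 12 × 435 = 5,220. Agrees.
- Total draw at 7%: 5,220/0.07 = 74,571. Agrees with the stated 74,570.
- Draw per stratum at 7%: 435/0.07 = 6,214. **Does not agree** with the stated 1,740.

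**Step 2. Test the two stated figures against each other.**

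- 12 × 1,740 = 20,880, not 74,570; the ratio is 74,570/20,880 = 3.6.
- 74,570/12 = 6,214, the per-stratum figure that the total implies.

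**Step 3. Allow for the rate being approximate.** Rates that round to 7% give 435/0.075 = 5,800 to 435/0.065 = 6,692 per stratum. None comes near 1,740.

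**Step 4. Look for a reading under which 1,740 is right.**

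| Reading | Arithmetic | Result |
|---|---|---|
| 25% participation | 435/0.25 = 1,740 | Exact, but this is the MAP-Z rate |
| Net enrolment per cluster | 4 × 435 = 1,740 | Exact, but this counts people enrolled, not drawn; the draw per cluster at 7% would be 1,740/0.07 = 24,857 |
| Age group within each of the 10 oblasts (40 cells) | 40 × 1,740 = 69,600 | Not 74,570; at 7% it yields 4,872, short of 5,220; and the section defines strata by cluster |

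No reading makes both figures in the MAP-U sentence correct.

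**Step 5. Size of the effect if 1,740 were drawn per stratum.** Half-width = 1.96 × √(0.24/n).

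| | As planned | If 1,740 are drawn |
|---|---|---|
| Enrolled per stratum | 435 | 1,740 × 0.07 = 121.8 |
| After 15% attrition | 369 | 121.8 × 0.85 = 103.5 |
| Enrolled in total | 5,220 | 12 × 121.8 = 1,462 |
| Half-width, enrolled | ±4.6% | ±8.7% |
| Half-width, after attrition | ±5.0% | ±9.4% |

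The article also claims ±6% to ±7% when cells are split further by sex. With an even split, half-widths grow by √2 = 1.414. The planned sizes then give ±6.5% (4.6 × 1.414) to ±7.1% (5.0 × 1.414), in line with the claim. A draw of 1,740 would give ±12.3% (8.7 × 1.414) to ±13.3% (9.44 × 1.414).

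**The case against.** The arithmetic is not open to dispute, but four fair points can be made against its weight.

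First, the loss of precision is conditional. The correct total stands in the same sentence as the wrong per-stratum figure, and nothing in the article shows that 1,740 was the number used. The paragraph that describes MAP-U sampling gives no count at all. This stands: if 74,570 people were drawn in equal strata, the error is one of reporting only.

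Second, the origin of 1,740 cannot be proved. It matches the MAP-Z invitation figure, but also the net enrolment for one cluster. In addition, ten times 1,740 is 17,400, the MAP-U inclusion target in the abstract, so the number could be left over from a design built on the ten oblasts. This stands as a caution about cause. The contradiction and its correction rest on the MAP-U inputs alone.

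Third, correcting one figure does not make the whole article consistent. The abstract's 17,400 people from Ukraine matches neither 5,220 net nor 74,570 drawn. That is true, but it is a separate inconsistency and does not alter the draw that follows from the inputs in the sample size section.

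Fourth, baseline was to start in March 2024 and the article refers to participants included up to 30 June 2024, so draws had presumably been made. This is a reason to check them, not a reason to leave the figure as it is.

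**Conclusion.** The concern holds. On the stated inputs (435 enrolled per stratum, 12 strata, about 7% participation), the MAP-U draw is about 6,214 per stratum. The stated total of 74,570 is right and the stated 1,740 per stratum is wrong, too small by a factor of 3.6.

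If the per-stratum figure were followed, each stratum would enrol about 122 people, with about 104 left after attrition. The half-width at 40% prevalence would be ±8.7% to ±9.4% instead of ±5%. That consequence assumes simple random sampling within strata and participation of 7% in every stratum, as the plan's own calculation does. It also depends on which of the two figures governed the draw, which the article does not reveal. A carry-over from the 25% MAP-Z rate is the most natural explanation, but it is an inference. The figure should be corrected in any case, because it is the per-stratum sampling number for the main cohort.

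**What to change.** In Sample Size Considerations and Calculation, replace the MAP-U per-stratum draw of 1,740 with about 6,214 per stratum, about 74,570 in total. If the per-stratum figure is to be rounded up so that 435 are expected at 7%, use 6,215 and change the total to 12 × 6,215 = 74,580. Keep 1,740 only for the MAP-Z age groups, where it follows from 25% participation.

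Check the sampling records to see which number was used in the draws already made, and top up any stratum that was under-drawn. While the section is open, confirm the intended net MAP-U target and reconcile it with the 17,400 in the abstract.

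The text correction costs one figure and, with the 6,214 option, leaves the stated total unchanged. Further cost arises only if the records show that 1,740 was drawn: about 6,214 − 1,740 = 4,474 additional people per stratum would then have to be drawn and approached.

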## Results

Detailed results and analyses of the mental health of the Ukrainian population will be presented and discussed in subsequent publications.

## Discussion

The current war in Ukraine undoubtedly causes enormous suffering, with an estimated 10 million people in Ukraine possibly experiencing adverse mental health effects [8]. The war has triggered an international response and prompted numerous national and international relief and crisis mitigation efforts for mental health. In the absence of a robust mental health monitoring system, it remains uncertain whether such relief efforts effectively support those in need, both now and in the future. Thus, establishing a comprehensive mental health surveillance system is essential to provide actionable insights for policymakers, national and international humanitarian agencies, healthcare providers, and communities.

While starting from solid and practice-tested methodologies and platforms, this study will also create key insights for authorities and scientific communities. This will provide vital learnings about establishing, scaling up and maintaining population-based monitoring studies under adverse conditions - a need that is clear from the lack of pertinent scientific literature and best practices. Furthermore, the monitoring system will enable epidemiologists and mental healthcare providers to leverage technological advances, examine their usefulness and implement novel digital tools to further expand into hard-to-reach subgroups. From the perspective of implementation science for digital health, the MAP study will provide novel insights into the acceptability, usability, scalability, and efficiency of conducting large scale, representative digital mental health surveillance effort during an ongoing war-time situation. Our study protocols and tools will directly inform needed best-practices for similar endeavours and provide guidance for epidemiologists and health researchers around the world seeking to repeatedly measure mental health outcomes in crisis situations (e.g., political conflict, mass migrations, climate disasters) by use of open-source tools.

Through our strong, existing collaboration between Swiss, Ukrainian and international scientists and policymakers, the necessary science-to-policy communication lines are in place to use our results – as they become available, uploaded to the online platform – to inform and guide decision-makers worldwide (i.e., public health officials, NGOs, humanitarian organizations).

Data on the prevalence of the four mental health conditions can serve as a basis for evidence-based policymaking and service implementation. Local, regional, and national policymakers will be better equipped to make informed decisions regarding resource allocation to regions in need of increased mental health support or to population groups requiring tailored mental health services. International humanitarian organizations operating in Ukraine can use our results to appropriately channel mental health services to target populations and (re)allocate funding for mental health spending. MAP findings can contribute to improving access to mental health services, as results can inform planning new mental health programs and expansion or adaptation of existing programs according to population needs. Results can also support the development of specialized training programs for professionals, especially in war and post-war areas. Furthermore, MAP will foster community support and promote mental health awareness. Reducing stigma around mental health is crucial to improve support and access to health services during and after the war.
